## Abstract

**Background:**

Non-muscle-invasive bladder cancer (NMIBC) is the most common neoplasm of the urinary tract and requires life-long invasive surveillance to detect disease recurrence. Currently, there are no effective oral therapies that delay disease recurrence or progression. We recently demonstrated that in mice, metformin accumulates unchanged in the urine. Urothelial cells are exposed to metformin concentrations ~ 240-fold higher than in serum. This was effective in the treatment of mouse bladder cancer models.

**Methods:**

We describe the protocol of a multi-centre, open-label, phase II clinical trial of metformin in up to 49 evaluable patients with intermediate-risk NMIBC with the aim to determine the overall response to administration of oral metformin for 3 months on a marker tumour deliberately left following transurethral resection of multiple, papillary NMIBC tumours. All patients will receive metformin orally at doses up to 3000 mg per day. Metformin treatment will start within 2 weeks following transurethral resection of all tumours except one marker lesion. After 3 months of metformin treatment, the effect of metformin on the marker lesion is evaluated by cystoscopy and biopsy under anaesthesia. Residual tumour, if present at this evaluation, will be resected. In case of complete disappearance of the marker lesion, the former tumour area will be biopsied. The primary outcome is the complete response rate of the marker lesion, as determined by decentralised scoring of pre- and post-treatment cystoscopy images by expert independent urologists. Secondary outcomes are the partial response rate, overall safety of metformin and the duration of the time to recurrence.

**Discussion:**

Preclinical studies show the potential role of oral metformin treatment in the management of NMIBC. It could offer an alternative to current adjuvant intravesical treatment. If positive, the reported results of this study could warrant further phase III trials to compare the efficacy of metformin against current treatments of intravesical installations with chemotherapy or Bacillus Calmette-Guérin (BCG).

**Trial registration:**

This trial is registered in ClinicalTrials.gov under NCT03379909.

## Background

Non-muscle-invasive bladder cancer (NMIBC) is the most common neoplasm of the urinary tract [1]. Despite current treatments, i.e. transurethral resection followed by adjuvant intravesical treatment with Bacillus Calmette-Guérin (BCG) immunotherapy or mitomycin C chemotherapy, it is still associated with a high risk of recurrence and/or progression [2]. The need for life-long invasive surveillance and treatment results in a high patient burden and puts NMIBC among the most expensive cancers to treat on a per-patient basis, which represents a major public health challenge. Therefore, the development of a safe, low-cost, and orally active drug for preventing recurrence and progression of NMIBC is a priority in urologic oncology.

There were ~ 3750 new cases of NMIBC in The Netherlands in 2018. The incidence is rising, from 10 new cases per 100,000 person-years in 1990 to 24 new cases per 100,000 person-years in 2018 (www.cijfersoverkanker.nl). Bladder cancer is the fifth most prevalent malignant disease for men and the tenth among women, and occurs mainly in the middle-aged and elderly [1, 3, 4]. NMIBC accounts for 70–80% of bladder cancers at first presentation. Stages Ta-T1 make up the majority of cases, with 5–10% diagnosed as primary carcinoma-in-situ (CIS), while a small percentage of patients presents with both. Recurrence rates following transurethral resection of the bladder tumour (TURB) vary from 30% for a single papillary tumour to over 90% in case of multiple tumours [4]. CIS has been viewed as both an aggressive neoplasm with high probability of invasion and alternatively as having limited biologic capacity to invade. The unpredictability of both papillary and CIS bladder tumour progression has led to the widespread use of adjuvant intravesical therapy, both in controlling existing tumours (therapy) and in preventing tumour recurrence (prophylaxis) [5].

### Metformin as an anti-cancer drug

Metformin is a widely used, inexpensive and safe drug that is first-in-line for the treatment of diabetes mellitus type 2 (T2DM). Substantial laboratory evidence supports the hypothesis that metformin has antineoplastic activity [6]. Moreover, epidemiologic studies have suggested that metformin reduces the occurrence, recurrence and progression of NMIBC in patients with T2DM, as compared with T2DM patients not treated with metformin [7–10]. While there are many ongoing trials of metformin for various indications in oncology, metformin has not been able to improve patient survival so far in any type of cancer [11–13]. One explanation could be that metformin fails to accumulate to a sufficient concentration in tissues to exert sufficient antineoplastic effects. In support of this, many in vitro studies show direct antiproliferative actions of metformin at millimolar concentrations [14–20], but after oral administration of metformin the highest attainable serum concentrations in vivo are in the micromolar range [11, 21].

Metformin is excreted unchanged in the urine and mice studies have shown that following oral dosing, the urothelium is exposed to urine metformin concentrations that are ~ 240-fold higher than in the circulation [18]. This resulted in improved survival, reduced urinary tract obstruction and reduced bladder weight of NMIBC-bearing mice [18]. In humans, metformin is also excreted unchanged in the urine, where concentrations are > 100-fold higher compared to the serum [22]. Thus, from a pharmacokinetic perspective, NMIBC is particularly interesting for clinical trials to evaluate metformin as an antineoplastic agent. Molecularly, metformin inhibits bladder cancer cell proliferation by various mechanisms, such as activation of AMPK and inhibition of mTOR [14–18] and inhibition of STAT3-mediated pathways [19, 20]. These anti-cancer properties of metformin were observed both *in vitro* [14] and intravesically in vivo [16–20] and both as metformin monotherapy [18] as well as in combination with other anti-cancer therapeutics, such as cisplatin [16] and gefitinib [17]. Of note, metformin markedly prolonged the survival of mice that were genetically engineered to develop bladder cancer [18].

### Leaving a marker lesion to study NMIBC response

A problem in the management of NMIBC is the frequency and multiplicity of tumour recurrence and the primary concern is, therefore, the efficacy of adjuvant therapy in delaying or preventing this recurrence. Previous studies have demonstrated that the ablative activity of intravesical therapy relies upon the response of Ta/T1 tumours remaining in the bladder, but these are confounded by the presence of multiple tumours of indeterminate number, size and characteristics [23]. The response rate observed for any drug can, therefore, vary because of this heterogeneity. Thus, it is recognized, though not universally accepted, that a marker lesion procedure is the most objective way of conducting phase II studies using novel agents for the treatment of Ta/T1 NMIBC lesions, before initiating large-scale registration trials [23]. All agents that have proven to be beneficial in prophylactic studies also have an ablative effect leading to a complete response of the marker lesion in up to 50–60% [23]. Several points concerning the safety of a marker lesion study can be made. First, prognostic factor analyses performed by the European Organisation for Research and Treatment of Cancer (EORTC) and the Medical Research Council (MRC) have shown that the likelihood of progression to muscle invasive bladder cancer (MIBC) in patients with multiple low-grade, intermediate risk NMIBCs is 0–2% and treatment with unproven agents is, therefore, acceptable [24]. Second, in a systematic review including 23 studies leaving a marker lesion in more than 1200 patients, 7 patients (0.6%) showed progression to muscle invasive bladder cancer (MIBC) [23]. However, progression was only seen in studies that included patients with a high-risk prediction score for NMIBC progression. Although it is unknown whether the progressed patients indeed had high-risk NMIBC, it is very likely that marker lesion experiments are safe in patients with low-, and intermediate-risk NMIBC. Third, if NMIBC is considered a pan-urothelial disease then clearly tumour cells or their precursors remain in the bladder after a visibly complete resection. In clinical studies in patients with a solitary Ta/T1 tumour, 5–20% of patients had a tumour at 4 weeks following a supposedly complete resection [25, 26]. A marker lesion procedure requires 2 cystoscopy procedures within a relatively short timeframe (one before [which is also performed in the standard of care] and one at the end of study treatment) and the extra cystoscopy can thus aid in the resection of any additional or persisting tumours that were not recognized at the first cystoscopy procedure. Fourth, before embarking on a larger-scale phase III trial, this approach prevents that many patients are exposed to a possible inferior treatment.

### Hypothesis and outlook

To summarise, the investigation of metformin in patients with NMIBC is warranted by several *in vivo* studies [16–20] and epidemiological evidence [7–10] demonstrating that metformin reduces bladder cancer risk, recurrence and progression in diabetic patients. Critically, it is likely that NMIBC cells are exposed to efficacious metformin concentrations because metformin accumulates unchanged in the urine and this exposes urothelial cells to metformin concentrations that are ~ 240-fold higher than in the serum [18]. Combined, these data provide a strong rationale for a phase II clinical trial of high-dose oral metformin in the treatment of NMIBC. We hypothesise that oral metformin administration results in therapeutic metformin concentrations in the urine and that this leads to tumour response of a NMIBC marker lesion that was deliberately left in situ*.*

## Methods/design

### Overall study design

This ‘*Phase II study of oral metformin for intravesical treatment of non-muscle-invasive bladder cancer*’ (TROJAN) study is a nonrandomized, open-label, multi-centre phase II clinical trial with oral metformin treatment in patients with intermediate-risk NMIBC. Patients will be enrolled at four hospitals in The Netherlands (the Amsterdam UMC in Amsterdam, the Jeroen Bosch Ziekenhuis in ‘s-Hertogenbosch, the RadboudUMC in Nijmegen and the Sint Franciscus Hospital in Rotterdam). This is a marker lesion study, meaning that in NMIBC patients undergoing TURB, a marker lesion will be deliberately left in the bladder. Patients will be treated with metformin for 3 months. Subsequently, the response on the marker lesion will be determined in a second TURB and the marker lesion is resected or (in case of a complete response) the area of the former marker lesion will be biopsied. After the second TURB, patients may choose to continue with metformin treatment.

### Objectives

#### Primary objective

The primary objective is to determine the complete response rate after administration of oral metformin for 3 months. This is assessed using a marker tumour deliberately left following transurethral resection of NMIBC lesion(s).

#### Secondary objectives

To determine the partial response rate following administration of oral metformin for 3 months in a marker tumour deliberately left following transurethral resection of NMIBC lesion(s);To determine the time to recurrence;The safety of metformin in this population;Quality of life during metformin treatment using two questionnaires (SF-36 and EORTC NMIBC-24).

#### Exploratory objectives

The effect of metformin on tumour biology markers in biopsies or tumour resection tissue taken before and after study treatment;The pharmacokinetic analysis of metformin levels in urine and serum;In case of promising results: a preliminary economic evaluation to estimate potential cost savings that could be achieved using metformin in NMIBC patients.

### Trial end points

#### Primary end points (outcomes)

The primary outcome is the complete response rate after 3 months of treatment with metformin. Evaluable patients are those who have received at least 500 mg metformin twice daily for one week and who undergo a cystoscopy for marker lesion removal. Primary study parameters are:
Complete response: complete disappearance of the marker lesion, as confirmed by negative biopsy at the marker lesion site, the absence of new tumours at other sites and a negative bladder washout cytology;No response: marker lesion persistence or the appearance of new lesions with stage T1 or less.

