### Participants

In brief, this trial will enrol 49 eligible patients with NMIBC. All inclusion and exclusion criteria are listed in Table 1. The sample size is based on a power analysis described under Statistical methods.

**Table 1 Tab1:** Inclusion and exclusion criteria

Key inclusion criteria	
• Age ⩾18 years. • Patients with primary or recurrent multiple histologically confirmed Ta or T1 (non-muscle invasive), G1 or G2 (low-grade) urothelial carcinoma of the bladder with no evidence of carcinoma in situ. • Patients must have at least 2 lesions, but no more than 10. • The resected lesions must contain detrusor muscle to confirm a Ta/T1 disease. • All visible lesions must be completely removed by transurethral resection at entry to the study, except for an untouched marker lesion measuring 0.5–1.0 cm in its greatest dimension. • Bimanual examination immediately following transurethral resection under anaesthesia should be carried out and no mass should be felt. • Adequate renal function (creatinine < 150 μmol/L and/or an eGFR > 60 ml/L). • Adequate liver function (bilirubin < 1.5 times upper limit of normal, ALAT or ASAT < 2.5 the upper limit of normal). • Eligible patients must be fully informed of the investigational nature of the study and written signed informed consent must be obtained prior to any study specific investigations. • Mentally, physically, and geographically able to undergo treatment and follow up.	
Key exclusion criteria	

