### Dose of study drugs and dose adjustments

All patients will receive metformin orally in a starting dose of 500 mg once daily and, if well tolerated, this will be increased to 500 mg twice daily in the second week, 1000 mg twice daily in the third week and, with a good renal function, eventually to a maximum of 3000 mg per day. This highest metformin dose is reserved to those with an estimated glomerular filtration rate (eGFR) of ≥60 mL/min to reduce the risk of lactic acidosis. Based on toxicity data from patients with T2DM, we expect that 2550 mg of metformin (850 mg three times daily) is a realistic maximum tolerable dose in most patients with an eGFR of ≥60 mL/min [27]. This dosing schedule conforms with the metformin label from the US Food and Drug Administration in the treatment of T2DM and the purpose of the stepwise dose increase is to reduce gastro-intestinal side effects [28]. Doses will be reduced for haematological and other adverse events. Dose adjustments are to be made according to the system showing the greatest degree of toxicity. Examples of metformin dose adjustments due to frequently occurring adverse events are shown in the Additional file 1**.**

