### Toxicity monitoring and adverse events

Adverse events will be graded using the CTCAE version 4.03. The major adverse effects of metformin, which may limit the maximum tolerable dose, are of gastro-intestinal nature, such as nausea, vomiting, diarrhoea, abdominal discomfort and loss of appetite. A rare but serious adverse event that can occur during metformin treatment is lactic acidosis [29]. This life-threatening condition is caused by accumulation of metformin. Risk factors include a combination of old age, doses over 2000 mg per day and renal impairment, either due to chronic renal impairment or due to acute renal failure as the result of dehydration, shock or the intravenous administration of iodinated contrast agents. The estimated prevalence of lactic acidosis is < 5 cases per 100,000 patient years [30].

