### Statistical methods

The patient sample size in the clinical trial (*n* = 49) is based on a two-part trial design:
Part 1: Initially, 13 patients will be treated. If no responses are seen in the first 13 consecutive, evaluable patients, the probability of a response rate of ≥30% in the overall NMIBC patient population is < 1% (type II error) and the trial shall be terminated.Part 2: If one or more responses are seen in the first part, the study will continue until the enrolment of 49 evaluable patients is met. This allows to establish a response rate of 50% with a power of 80%, an α error of 5%, and to reject with the same power a response rate of < 30%.

According to statistical review, the analysis after part 1 is not an interim analysis and additional correction is not necessary. For the secondary endpoint concerning partial responses, the tumour dimensions captured by decentralised measurements from cystoscopy images before and after the metformin treatment will be compared using the paired samples *t*-test.

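### The complete response rate is taken over evaluable patients only, which raises it above the rate among all patients who start metformin with a marker lesion in place

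*Protocol article*

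**What the plan says.** Under Primary end points, the article states: "The primary outcome is the complete response rate after 3 months of treatment with metformin". The denominator follows at once: "Evaluable patients are those who have received at least 500 mg metformin twice daily for one week and who undergo a cystoscopy" for removal of the marker lesion. Complete response requires "complete disappearance of the marker lesion, as confirmed by negative biopsy at the marker lesion site", together with no new tumours elsewhere and a negative washout cytology.

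Under Dose of study drugs, patients start at 500 mg once daily. If that is well tolerated, "this will be increased to 500 mg twice daily in the second week". On this schedule the dose condition is met at the end of week 2 at the earliest.

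Under Statistical methods, the early stopping rule uses the first 13 evaluable patients, and after that "the study will continue until the enrolment of 49 evaluable patients is met". The design is meant to establish "a response rate of 50% with a power of 80%, an α error of 5" per cent, and to reject a rate below 30%. The Abstract also counts up to 49 evaluable patients. Participants instead says that "this trial will enrol 49 eligible patients with NMIBC".

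Toxicity, by contrast, is evaluated in every patient from the first metformin treatment (Secondary end points). The article states no response rate for all treated patients and no rule for scoring those who are not evaluable.

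**The concern.** Both conditions for entering the denominator are decided after treatment begins. A patient can fail them by stopping very early or by never having the cystoscopy. The article allows voluntary withdrawal (Harms) and describes the main adverse effects as ones "which may limit the maximum tolerable dose, are of gastro-intestinal nature", so some exclusions may be linked to tolerability. Each of these patients had a tumour deliberately left and took the drug, and those without a cystoscopy cannot meet the definition of complete response.

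There is no control arm in which the same selection would operate. The filtered rate is compared with a fixed 30%. The article also uses the expected 50% beyond the evaluable set: its economic evaluation applies it to NMIBC patients generally, and its Discussion considers metformin as a replacement for instillations. Those uses need the rate among patients who start the drug.

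**Working it through.** **Inputs from the article.** Null rate 0.30, target rate 0.50, alpha 5% (sidedness not stated), power 80%, n = 49 evaluable, early stop at 0 of 13.

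**Assumption.** A share *d* of treated patients is not evaluable, with *d* = 5%, 10%, 15% or 20%. The article gives no figure.

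**Step 1: reproduce the design.** With X binomial(49, p), the cut-off X ≥ 22 gives P(X ≥ 22 | 0.30) = 1.9% and P(X ≥ 22 | 0.50) = 80.4%. This matches an exact two-sided 5% test (2.5% in the upper tail) with 80% power, so 49 reproduces. For the early rule, 0.7^13 = 0.0097, which matches the stated error below 1%. A one-sided 5% reading would give a cut-off of 21 of 49, with 3.8% error and 87.4% power.

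**Step 2: effect of the filter.** If excluded patients are all non-responders and the all-treated rate is 0.30, the evaluable rate is 0.30/(1 − *d*). For *d* = 10%, 0.30/0.90 = 33.3%.

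| *d* | Evaluable rate | P(≥22 of 49) | P(≥21 of 49) |
|---|---|---|---|
| 0% | 30.0% | 1.9% | 3.8% |
| 5% | 31.6% | 3.5% | 6.4% |
| 10% | 33.3% | 6.1% | 10.5% |
| 15% | 35.3% | 10.6% | 16.9% |
| 20% | 37.5% | 17.8% | 26.3% |

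**Step 3: a just-positive result.** 22/49 is 44.9%. Reaching 49 evaluable patients takes N = 49/(1 − *d*), rounded up: 52, 55, 58 or 62 treated. With the excluded patients as non-responders, 22/N is 42.3%, 40.0%, 37.9% or 35.5%. The exact upper-tail p-value against 30% is 0.040, 0.073, 0.121 or 0.209. All of these exceed 0.025, so the choice of denominator alone can reverse a borderline conclusion.

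**Step 4: power of an all-treated test.** Take N as fixed and use the smallest cut-off with an upper tail of at most 2.5% at 0.30. If 50% is the all-treated rate, power is P(X ≥ cut-off | N, 0.50). If 50% holds only among evaluable patients, the all-treated rate is 0.50(1 − *d*).

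| *d* | N | Cut-off | Power, 50% all-treated | Power, 50% evaluable only |
|---|---|---|---|---|
| 5% | 52 | 23 | 83.4% | 72.9% |
| 10% | 55 | 24 | 86.0% | 63.1% |
| 15% | 58 | 25 | 88.1% | 51.3% |
| 20% | 62 | 27 | 87.4% | 32.7% |

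**Step 5: the 13-patient rule.** If it were moved to all treated patients while the evaluable rate is 30%, the chance of 0 of 13 would be (1 − 0.30(1 − *d*))^13. This is 1.3% at *d* = 5%, 1.7% at 10% and 2.8% at 20%, above the stated limit of 1%.

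**The case against.** The strongest defence is that the trial asks whether metformin has ablative activity on a marker lesion. An evaluable set is a recognised phase II choice for that question. For the quantity the article tests, the rate in evaluable patients, the design has the error and power it claims. That stands: the inflation in Step 2 is error against an all-treated rate of 30%, and a reader who infers that the stated type I error is wrong would go too far. It does not remove the concern, because the result is to be read more widely than the evaluable set.

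Three other inferences also go too far.

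- A reader might infer that no excluded patient could be a complete responder. The two conditions are joined by "and", so a patient who misses only the dose condition may still have the cystoscopy and biopsy and could be a documented responder. Only those without a cystoscopy cannot.
- A reader might infer that early failures in general are dropped. Patients who pass the dose threshold and stop later remain if they have the cystoscopy. The definition sets no time window, so an early cystoscopy for failure also keeps them in.
- A reader might infer that exclusions of 10% to 20% are expected. Nothing in the article supports a figure. Its remark on gastro-intestinal effects concerns the maximum tolerable dose, and the stepwise increase is meant to reduce such effects.

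A supportive all-treated analysis might stand in a separate analysis plan. The article itself, however, fixes the evaluable denominator and builds the sample size on it. The wording in Participants is a minor inconsistency: the sentence is a summary that refers to Statistical methods for the sample size.

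**Conclusion.** The point holds as a statement about direction: leaving out patients who start metformin but never have the cystoscopy raises the reported complete response rate above the all-treated rate. The size is conditional. For 5% to 20% excluded, all non-responders, a true 30% appears as 31.6% to 37.5%, and the chance of at least 22 of 49 rises from 1.9% to between 3.5% and 17.8%. The excluded share is assumed and the cut-off is inferred. For a given share these figures are the upper end, since any documented response among patients excluded only on dose would reduce them. If very few patients are excluded, the effect is small.

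The documents do not support the view that the change is one of wording only, or that the 13-patient rule should move to the new denominator as well (Steps 4 and 5).

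**What to change.** 1. Base the final complete response rate, and its exact binomial test against 30%, on all patients who had a marker lesion left and took at least one dose of metformin.
2. Score every patient with a cystoscopy by the actual result, whatever dose was reached. Count patients without one as non-responders.
3. Keep recruiting to 49 evaluable patients, and report the evaluable-set rate as supportive.
4. Leave the 13-patient rule on evaluable patients, so that its stated error below 1% still holds.
5. State the cut-off or sidedness of the final test, and reconcile the 49 eligible patients in Participants with the 49 evaluable in the Abstract and Statistical methods.

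Cost: all treated patients are already followed for toxicity, so no new assessments are needed. The reported rate becomes less favourable. Power stays at 83% or more if 50% is the all-treated rate. If 50% holds only among evaluable patients, power drops below 80%, to about 73% at 5% excluded and 63% at 10%. The sponsor should say which population the 50% refers to and, if it is the evaluable one, either accept the lower power or revisit the sample size.
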